## Abstract

**Methods::**

A prospective randomized controlled clinical trial design was used to study the efficacy and safety of MT in the treatment of CP. One hundred and twenty cases of CP patients will be recruited and randomly divided into experimental group and control group according to 1:1. The control group: sodium hyaluronate; experimental group: MT added on the basis of the control group. Both groups will receive standard treatment for 4 weeks and followed up for 3 months. And at the same time, pay attention to its efficacy and safety indicators. Observation indicators include: the visual analogue scale pain score; the Western Ontario and McMaster Universities Arthritis Index scores; the Lysholm scores, and Bristol scores, adverse reactions, etc. Data analysis was performed using SPSS 25.0 software.

**Discussion::**

This study will precisely evaluate the effectiveness and safety of MT in the treatment of CP. The results of this experiment will provide more reliable clinical basis for the selection of MT for patients with CP.

## 1. Introduction

Chondromalacia patellae (CP), also known as patellofemoral pain syndrome, anterior knee pain syndrome, patellofemoral joint syndrome, etc., was first proposed by Aleman.^[1]^ It is a degenerative disease of patellar cartilage, which is a common and main cause of knee pain. Most patients with this disease have different degrees of poor patellofemoral joint force line and (or) abnormal patellar motion track, making the lateral patella perennial high pressure, which can lead to the secretion of pain-causing inflammatory factors such as interleukin-6, causing pain and subsequent patellofemoral articular cartilage softening until gradual denudation. The prevalence of the disease in the general population is as high as 36.2%, especially in middle-aged patients aged between 30 and 40 years (up to 50%). The prevalence rate in women is higher, about twice that in men.^[2]^ This disease often occurs after strenuous exercise, which can lead to soft legs, joint swelling and pain, restricted movement and other symptoms. The pain is obvious after going upstairs and downstairs, climbing, squatting, kneeling and even sitting for a long time, which seriously affects the quality of life.^[3,4]^ Hence, CP has become a major global public health problem, and the effective treatment is of great significance.

CP is generally treated conservatively in the early stage of the disease, while surgical treatment is suitable for advanced patients. Through methods including cartilage transplantation and total knee replacement, the normal tissue structure around the patella can be restored and reconstructed, and finally the purpose of treating the disease can be achieved.^[5,6]^ The consensus released by the International Patellofemoral Research Center in 2018 believes that the key treatment of CP is exercise therapy and physical intervention,^[7]^ and its management should include an individual, multi-modes exercise and treatment method.^[8]^ Among all the treatment methods, manual therapy (MT) has occupied a certain advantage in clinical application due to its simple operation, obvious effect, small side effects, high safety and good economic effect.

Based on modern western medical theory, MT techniques include joint mobilization, manual stretching and trigger point dry needle. Many studies have found that joint mobilization is effective in pain reduction, while the most effective joint mobilization is aim at the knee joint complex directly rather than at the lumbar-pelvic region or other surrounding joints, although lumbar-pelvic manipulation can also improve patients’ pain and function.^[9–11]^ The use of traditional Chinese medicine massage to dredge the meridians and muscles around the knee joint and stimulate the relevant acupoints can also play vital roles in relieving pain and improving function.

In recent years, studies on the effect of MT for CP have increased at home and abroad, but its clinical efficacy is still unclear. Therefore, the purpose of our study is to precisely evaluate the advantages and disadvantages of MT in the treatment of CP in this randomized controlled trial.

## 2. Materials and methods

### 2.1. Study design

This is a prospective randomized controlled clinical trial studying the effects of MT on CP. This protocol follows the latest Consolidated Standards of Reporting Trials (2017) (flowchart is shown in Fig. 1) and Standard Protocol Items: Recommendations for Interventional Trials 2013 statement.

**Figure 1. F1:**
[figure not shown]
Study flow chart.

### 2.2. Ethics and registration

This research scheme is approved by the Clinical Research Ethics Committee of our hospital. This experiment has been registered om Chinese Clinical Trial Registry (registration number: ChiCTR2300068655). Before randomization, all patients needed to sign an informed consent form, and only patients who sign informed consent will be enrolled in the study. During the test, they are free to choose whether to continue the test at any time.

### 2.3. Patients

#### 1.2.3. Inclusion criteria.

Those who meet the diagnostic criteria of CP; age: ≥18 and ≤65 years old, regardless of gender; within 3 months before enrollment, they did not receive joint cavity injection treatment and did not take any drugs to treat CP; those who have certain communication and understanding ability, and can express their own will correctly; no other soft tissue and bone diseases of the knee joint; those who voluntarily accept corresponding treatment and can cooperate; no other serious nervous or mental diseases; and those who have signed the informed consent.

#### 2.2.3. Exclusion criteria.

Patients who suffer from acute systemic illness or acute swelling; patients who have severe impairment of limb function; patients with severe heart, lung, liver and kidney dysfunction; patients with local skin infection or ulceration; patients combined with severe mental illness; patients who are allergic to the drugs used in this study; and patients who are unable to understand the study protocol or unwilling after explanation.

#### 3.2.3. Elimination criteria.

Patients with serious adverse events or serious complications, which is not suitable for the next step; patients with poor compliance, affecting the judgment of efficacy and safety; the disease progresses during the treatment process, and the treatment plan needs to be changed; and for any reason, the subject asked to withdraw from the trial.

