### 2.4. Sample size calculation

According to the preliminary clinical trial, the total effective rate of MT combined with sodium hyaluronate was 93.4%, and that of sodium hyaluronate was 66.6%. Use PASS15.0 to estimate the sample size, adopt a superiority design, in which α = 0.05, β = 0.2, test power = 0.8, number of cases in experimental group: number of cases in control group = 1:1, boundary value = –0.4. According to the software calculation, the total sample size of the 2 groups was 110 cases. Taking into account the clinical shedding rate of about 10%, a total of 120 cases will be finally included. The included patients will be numbered according to the order of treatment and divided into the treatment group and the control group by completely random method, with 60 cases in each group.

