### 2.5. Interventions

This study will select patients who meet the study criteria by recruiting them at the hospital. A randomized controlled study will be conducted, in which sodium hyaluronate will be used in the control group and the experimental group will include MT exercise on the basis of the control group. If necessary, the attending doctor may adjust the treatment according to the patient’s condition, and all interventions will be recorded in detail for final outcome analysis. Efficacy assessors are not aware of the study plan, and data statisticians are not involved in study design and implementation. The health of each patient will be assessed before and after the treatment, including observational indicators, and all patients will be followed up by telephone.

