#### 2.6.2. Efficacy indicator.

Main efficacy indicators: total effective rate: (clinical control + significantly effective number + effective number)/total number of people × 100%. Clinical control: pain and other symptoms disappear, joint activity is normal, integral reduction ≥ 95%; significantly effective: pain and other symptoms disappear, joint activity is not limited, 70% ≤ integral reduction < 95%; effective: pain and other symptoms basically disappear, joint activity is slightly limited, 30% ≤ integral reduction < 70%; and ineffective: no significant improvement in symptoms such as pain and joint activity, integral reduction < 30%.

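### The elimination rule, read plainly, takes randomised patients out of the evaluation for post-randomisation events, so treatment failures can drop out of the total effective rate

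*Protocol article*

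**What the plan says.** The protocol article lists elimination criteria in section 3.2.3, separately from the inclusion and exclusion criteria. There are four grounds:

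- serious events: "Patients with serious adverse events or serious complications, which is not suitable for the next step";
- poor compliance and progression: "patients with poor compliance, affecting the judgment of efficacy and safety; the disease progresses during the treatment process", the latter where the treatment plan has to be changed;
- withdrawal: "for any reason, the subject asked to withdraw from the trial".

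Section 2.6.2 defines the main efficacy indicator, the total effective rate, as ("clinical control + significantly effective number + effective number)/total number of people × 100"%). It does not say whether the denominator is everyone randomised or everyone remaining. The failure category in the same section is "ineffective: no significant improvement in symptoms such as pain and joint activity, integral reduction < 30"%.

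Section 2.5 lets the attending doctor adjust treatment and says that "all interventions will be recorded in detail for final outcome analysis". Section 2.9 compares counts by chi-square test. Section 2.4 raises 110 patients to 120, 60 per arm, for shedding of about 10%.

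**The concern.** The grounds in 3.2.3 are met after randomisation, and some are closely tied to outcome. A patient whose disease progresses until the plan has to change would normally fall in the ineffective category of 2.6.2. Under 3.2.3 that patient is eliminated, and nothing in the article counts eliminated patients as failures or keeps them in the denominator. The compliance ground is justified by its effect on judging efficacy and safety, which is a reason about evaluability rather than about stopping treatment. It carries no threshold, so its use is discretionary.

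Removals need not be balanced. Sections 2.5.1 and 2.5.2 give control patients four weekly injections and MT patients the same injections plus a daily session of about 20 minutes for 4 weeks. At stake is whether the chi-square test compares the groups as randomised or groups selected by what happened to them afterwards.

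Sections 3.2.3 and 2.5 also need a clear boundary. A patient whose treatment is changed because of progression can fall under both, and the article does not say which applies.

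**Working it through.** **Inputs from the protocol article.** 60 per arm; effective rates 93.4% and 66.6%; α = 0.05; power 0.8; shedding about 10% (all 2.4). Chi-square test on counts (2.9).

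**Assumptions.** The fraction of failures eliminated, f in the MT arm and g in control, is given nowhere and is varied below. Sidedness is not stated; I use a two-sided 5% test, so 2.5% nominal in favour of MT.

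**Step 1: the plan's own figures.** 110/0.9 = 122.2, rounded up to 123, is close to the stated 120. The 110 itself could not be reproduced. A zero-margin two-sided comparison needs [1.96 × √(2 × 0.8 × 0.2) + 0.8416 × √(0.934 × 0.066 + 0.666 × 0.334)]² / 0.268² = 33.8, so 34 per arm or 68 in total. With the stated boundary of –0.4 the total is 8 to 12. That is a separate matter. Everything below uses 60 per arm and does not depend on 110.

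**Step 2: one arm.** With true rate p and a fraction f of failures removed, the expected rate among those kept is p / [p + (1 – p)(1 – f)], which exceeds p whenever f > 0. For p = 0.666:

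- f = 0.25: 0.666/0.9165 = 72.7%
- f = 0.30: 0.666/0.8998 = 74.0%
- f = 0.50: 0.666/0.8330 = 80.0%

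**Step 3: fixed counts, uncorrected chi-square.** About 10% of 120 is 12 patients.

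- No true effect, 40/60 in both arms. Removing 12 MT failures gives 40/48 v 40/60, or 83.3% v 66.7%, p = 0.0495. Removing 6 from each gives 40/54 in both, 74.1% v 74.1%.
- The protocol's effect, 56/60 v 40/60, difference 26.7 points. Removing 12 control failures gives 93.3% v 83.3%, difference 10.0, p = 0.10. Removing the 4 MT failures gives 100% v 66.7%, difference 33.3.

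The difference can therefore move either way.

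**Step 4: simulation.** 400,000 replicates. Successes are Bin(60, p) per arm, each failure is removed with probability f or g, and the chi-square test is applied to those kept.

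| True rates (MT v control) | f | g | Expected number removed | Significant in favour of MT |
|---|---|---|---|---|
| 66.6% v 66.6% | 0 | 0 | 0 | 2.5% |
| 66.6% v 66.6% | 0.30 | 0.30 | 6 + 6 | 2.5% |
| 66.6% v 66.6% | 0.30 | 0.20 | 6 + 4 | 5.0% |
| 66.6% v 66.6% | 0.25 | 0 | 5 + 0 | 10.6% |
| 66.6% v 66.6% | 0.50 | 0 | 10 + 0 | 34.8% |
| 93.4% v 66.6% | 0 | 0 | 0 | 97% |
| 93.4% v 66.6% | 0 | 0.30 | 0 + 6 | 84% |

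Numbers removed are 60 × (1 – p) × f or g; for example 60 × 0.334 × 0.5 = 10.

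**Step 5: cost of keeping everyone.** Suppose 10% per arm are eliminated unrelated to outcome and all count as failures. The rates become 0.9 × 93.4 = 84.1% and 0.9 × 66.6 = 59.9%. Power is Φ{[√60 × 0.2412 – 1.96 × √(2 × 0.72 × 0.28)] / √(0.8406 × 0.1594 + 0.5994 × 0.4006)} = Φ(1.02) = 84.6%.

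**The case against.** The strongest reply is that 3.2.3 never says eliminated patients leave the analysis. It stands with the eligibility criteria, not in 2.9, and three of its four grounds read like reasons to stop participation. The denominator in 2.6.2 is compatible with everyone randomised, and analysis sets may be defined in a document that is not shown. This stands in part: removal from the analysis is a reading, though the plain one given the heading and the compliance wording. The point is therefore the rule as written, not the absence of an analysis-set definition.

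Four stronger readings are tempting, and the article does not support them.

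- *All grounds are outcome-related, and progression is ineffective by definition.* Withdrawal and poor compliance can be unrelated to outcome. Only progression that needs a changed plan, and only serious events unsuitable for the next step, trigger the rule. Section 2.6.2 does not mention progression.
- *The adverse event rate is understated.* Section 2.6.3 counts symptoms during treatment, which can include those before elimination, and 2.8 provides safety monitoring of each participant. Nothing says that an event is deleted. An effect is possible but not shown.
- *Section 2.5 directly contradicts 3.2.3.* It says that interventions are recorded for the analysis, not that patients with adjusted treatment are kept in it. The boundary is unclear, which is less than a contradiction.
- *A 35% error rate is to be expected.* It needs half of the MT failures, only failures, and none in control to be removed. Likewise, at an assumed 85% v 66.6%, removing 30% of control failures cuts power from 67% to 31%, but 85% is not a protocol figure. At the protocol's own rates power stays above the planned 80%.

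**Conclusion.** The concern holds in a limited form. As written, 3.2.3 can take randomised patients out of the efficacy evaluation for events after randomisation, and some of them would normally be failures. Where failures are removed, that arm's effective rate is inflated; this follows from arithmetic alone. Bias in the group difference depends on unequal removal, which the different treatment burden makes plausible but which the documents do not quantify, and its direction cannot be fixed in advance.

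With no true effect, the false-positive rate in favour of MT ranges from nominal under equal removal, through about 5% at 30% v 20%, to about 11% or 35% when a quarter or a half of MT failures alone are removed. These figures rest on assumed elimination fractions, on removal of failures only, and on a two-sided 5% test. The heaviest case removes about 10 of 120 patients, within the shedding allowance, but it is an illustration and not a forecast.

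**What to change.** - State in 3.2.3 that the criteria govern stopping study treatment or participation, not leaving the analysis.
- For the total effective rate, analyse all randomised patients in their assigned group, with 60 per arm as the denominator. Count patients eliminated for progression, or without an outcome assessment, as ineffective.
- Keep eliminated patients in the adverse event count.
- Use the set without eliminated patients only as a sensitivity analysis.
- Reconcile 3.2.3 with 2.5, so that it is clear how patients whose treatment is changed are handled in the analysis.

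The cost is rewording 3.2.3, 2.6.2 and 2.9, and slightly lower reported effective rates. At the planned 120 patients it is affordable: the power of about 85% in step 5 compares with 96.5% from the same formula at 93.4% v 66.6% and no losses, and still exceeds the 80% target. The wording should be settled before outcomes are known.

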### 2.4. Sample size calculation

According to the preliminary clinical trial, the total effective rate of MT combined with sodium hyaluronate was 93.4%, and that of sodium hyaluronate was 66.6%. Use PASS15.0 to estimate the sample size, adopt a superiority design, in which α = 0.05, β = 0.2, test power = 0.8, number of cases in experimental group: number of cases in control group = 1:1, boundary value = –0.4. According to the software calculation, the total sample size of the 2 groups was 110 cases. Taking into account the clinical shedding rate of about 10%, a total of 120 cases will be finally included. The included patients will be numbered according to the order of treatment and divided into the treatment group and the control group by completely random method, with 60 cases in each group.

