### 2.9. Statistical analysis

In this study, SPSS25.0 statistical analysis software (IBM, Amenk, NY) will be used for data analysis. If the measurement data meet the normal distribution, independent-sample *t* test will be used between groups and paired-sample *t* test will be used within groups; if not, non-parametric test will be used and the results will be expressed in quartiles; the count data were tested by chi-square. The incidence of adverse events is compared by chi-square test. *P* < .05 is statistically significant.

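### The boundary of –0.4 in Section 2.4 fits neither the superiority label nor the planned chi-square test, and the stated 110 patients do not follow from the stated inputs

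*Protocol article*

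**What the plan says.** Section 2.4 of the protocol article takes its rates from a preliminary trial: "the total effective rate of MT combined with sodium hyaluronate was 93.4"%, "and that of sodium hyaluronate was 66.6"%. It then says the PASS calculation will "adopt a superiority design, in which α = 0.05, β = 0.2, test power = 0.8", and goes on to "number of cases in experimental group: number of cases in control group = 1:1, boundary value = –0.4". From this it reports 110 patients in total, raised to 120 for a dropout of about 10%, with 60 per group.

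The section does not say whether the boundary is a difference, a ratio or an odds ratio, which arm is subtracted from which, or whether α is one- or two-sided.

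Section 2.6.2 names the total effective rate as the main efficacy indicator, so a higher value is better. Section 2.9 says of such data that "the count data were tested by chi-square", with P < .05 as the significance rule. It mentions no boundary.

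**The concern.** For a rate where higher is better, superiority means ruling out a difference (MT minus control) of zero or less, or of some positive margin or less. A boundary of –0.4 on that scale belongs to a non-inferiority question with a very wide margin. With the subtraction reversed it becomes a superiority margin larger than the effect the plan assumes. The chi-square test in Section 2.9 asks a third question: is there any difference?

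Two things are at stake. The sample size is the only place where a margin for the main comparison is stated, so a reader cannot tell from the article which hypothesis the trial was sized for, or verify the 110. And a margin in one section beside a zero-difference test in another leaves two candidate success criteria on the page.

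**Working it through.** **Inputs.** From Section 2.4: MT plus sodium hyaluronate 0.934; control 0.666; α = 0.05; power 0.80; 1:1 allocation; boundary –0.4; stated total 110 (55 per arm); final total 120 (60 per arm). Sidedness is not stated, so both are shown.

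Assumed difference: 0.934 – 0.666 = 0.268. 
Unpooled variance sum: 0.934 × 0.066 + 0.666 × 0.334 = 0.0616 + 0.2224 = 0.2841. 
(z for α + z for power)²: (1.645 + 0.842)² = 6.18 at one-sided 0.05; (1.960 + 0.842)² = 7.85 at one-sided 0.025.

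**1. Boundary –0.4 on MT minus control.** Distance from the boundary: 0.268 + 0.4 = 0.668. 
n per arm = 0.2841 × 6.18 / 0.668² = 3.9, so 4 (total 8). 
At one-sided 0.025: 0.2841 × 7.85 / 0.668² = 5.0, so 5 (total 10). 
If the two rates are instead taken as equal at 66.6%, the totals are 36 and 44. None is 110.

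**2. Boundary –0.4 on control minus MT.** This is +0.4 on MT minus control. The distance is 0.268 – 0.4 = –0.132, so the assumed effect lies inside the null hypothesis and no sample size gives 80% power. The formula returns 202 or 256 only because it squares a negative distance. At 60 per arm the standard error is √(0.2841/60) = 0.0688, and the chance of success at one-sided 5% is P(Z > 1.645 + 0.132/0.0688) = P(Z > 3.56), about 0.0002.

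**3. Boundary 0, as in Section 2.9.** Mean rate 0.80, so the pooled term is √(2 × 0.80 × 0.20) = 0.5657, and the unpooled term is √0.2841 = 0.5330. 
Two-sided 0.05, power 0.80: n = (1.960 × 0.5657 + 0.842 × 0.5330)² / 0.268² = 33.8, so 34 per arm (total 68). With continuity correction it is 41 per arm (total 82). One-sided 0.05 gives 54, or 68 with correction.

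**4. What 110 does match.** The step 3 formula at power 0.95: n = (1.960 × 0.5657 + 1.645 × 0.5330)² / 0.268² = 54.9, so 55 per arm, total 110. In reverse, the two-sided power without continuity correction is Φ((0.268 × √n – 1.960 × 0.5657) / 0.5330):

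| Per arm | Argument | Power |
|---|---|---|
| 55 | 1.649 | 95.0% |
| 60 | 1.815 | 96.5% |

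This match does not show which settings were used. It shows only that 110 and the stated "test power = 0.8" do not go together for a zero-difference test.

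**5. Other scales.** Reading 0.4 as a log odds ratio gives totals from 48 to 134, depending on sign and sidedness. The nearest to 110 is 106 (margin +0.4 in favour of MT, one-sided 0.05). On the log risk ratio, –0.4 gives 14 or 18, and +0.4 exceeds the assumed effect of 0.338. The arcsine method with boundary 0 gives 50 or 62. None returns 110.

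**The case against.** The strongest reply is that the boundary is merely a software input, possibly mistyped or misreported, and that it decides nothing. It appears once, in a list of PASS settings, and the only decision rule in the article is the chi-square at P < .05. The 8 to 10 patients found in step 1 themselves suggest that –0.4 on MT minus control was never the operative null. With 120 patients the planned test is well powered at the assumed rates, so the main conclusion is safe.

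Most of this stands, and it limits the point. A reader might infer that the plan would let MT be declared superior while up to 40 points worse than control. The documents do not support that. Under the test in Section 2.9, a large deficit for MT would be non-significant or would significantly favour control. The inference needs –0.4 as the success criterion, which no section states. On that hypothetical, with 60 per arm and control at 66.6%, an MT arm truly 20 points worse would pass 73% of the time (one-sided 5%) or 62% (one-sided 2.5%). Those figures describe a test the plan does not contain.

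It can also be said that on an odds-ratio scale, with the subtraction reversed, 0.4 would be an attainable superiority margin, and that 106 is close to 110. But the article names no such scale, the figure still differs, and the planned chi-square would not test that margin.

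What the reply does not remove is the conflict on the page: a superiority label, a boundary that does not fit it on the difference scale in either direction, a test that ignores it, and a total that the listed inputs do not produce.

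**Conclusion.** The sample-size statement is wrong as written. On the difference scale, –0.4 is either a 40-point non-inferiority bound (total 8 to 10) or a 40-point superiority margin that the assumed 26.8-point effect cannot meet. Neither is the zero-difference hypothesis that Section 2.9 tests, which needs 68 patients (82 with continuity correction) at two-sided 0.05 and 80% power. The stated 110 is not reproduced under either sign or under any of the alternative scales tried at 80% power.

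The consequence is an unverifiable calculation and a mismatch between the sizing and analysis hypotheses. It is not an underpowered trial or a test that rewards a worse treatment. The results rest on the assumed 93.4% and 66.6%, equal allocation and normal approximations. The identity of the intended boundary remains unknown.

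**What to change.** In Section 2.4:

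- Delete the boundary value.
- State the null hypothesis as a difference in total effective rate (MT minus control) of 0, at two-sided α = 0.05, tested by the chi-square in Section 2.9. Report the risk difference with its 95% CI.
- Restate the calculation. Deleting the boundary alone is not enough, because 110 would still disagree with 80% power. Keep 120 patients and give the power as about 95% at 55 per arm and 96.5% at 60 per arm under 93.4% versus 66.6%.

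The cost is a few sentences and a short amendment, with no extra patients.

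If the sponsor did intend superiority by a margin, the scale, direction, sidedness and justification must be given, the margin must lie below 0.268 on the difference scale, and Section 2.9 must test it. The size would then need rechecking: a margin of 0.10, taken only as an illustration, needs 126 patients (one-sided 0.05) or 160 (one-sided 0.025) at 80% power before dropout.

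### Section 2.4: the stated rates, α, power, –0.4 boundary and total of 110 are mutually inconsistent, and the text does not show which of them is wrong

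*Protocol article*

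**What the plan says.** Section 2.4 (Sample size calculation) takes its rates from a preliminary trial: "the total effective rate of MT combined with sodium hyaluronate was 93.4%, and that of sodium hyaluronate was 66.6" per cent. It says the calculation will "adopt a superiority design", with "α = 0.05, β = 0.2, test power = 0.8", equal allocation and a boundary value of –0.4. The result is given as "According to the software calculation, the total sample size of the 2 groups was 110 cases", and the allowance for loss as "Taking into account the clinical shedding rate of about 10%, a total of 120 cases will be finally included", 60 per group.

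The section does not say whether α is one- or two-sided, which way the difference is taken, or which test or variance formula was used. Section 2.9 (Statistical analysis) says count data are compared by chi-square at P < .05. That is a test of zero difference, with no margin.

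**The concern.** This is the trial's only sample-size justification. It gives rates, α, power, ratio and boundary together with the resulting N, so it can be recalculated. If N does not follow, the stated power cannot be relied on, and a reader cannot tell what difference the trial can detect.

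The direction of the error matters. On one reading the trial has more power than claimed. On another it has clearly less. The boundary raises a second problem: taken as experimental minus control, –0.4 asks only whether manual therapy is less than 40 points worse than control. Taken the other way, it asks whether control is less than 40 points worse than manual therapy. Neither is a claim that adding manual therapy is superior.

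**Working it through.** **Inputs (section 2.4).** Experimental rate 0.934, control rate 0.666, difference 0.268, α = 0.05, power 0.80, ratio 1:1, boundary –0.4. Sidedness and direction are not stated, so both options are tried. One-sided levels are 0.05 and 0.025, the latter being equivalent to two-sided 0.05.

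**Derived quantities.**
- Sum of variances: V = 0.934×0.066 + 0.666×0.334 = 0.0616 + 0.2224 = 0.2841; √V = 0.5330.
- Mean rate 0.800; pooled variance 2×0.8×0.2 = 0.320; square root 0.5657.

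**Formulae, n per arm, with D the distance from the assumed difference to the margin.**
- Pooled null variance: n = (z_α×0.5657 + z_β×0.5330)² / D²
- Unpooled: n = 0.2841×(z_α + z_β)² / D²
- Continuity correction: n_c = (n/4)×[1 + √(1 + 4/(nD))]²

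**Attempt to reproduce 110 in total at 80% power.**

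| Reading | D | Total N over the variants |
|---|---|---|
| –0.4, experimental minus control | 0.268 + 0.4 = 0.668 | 8–18 |
| –0.4, control minus experimental | 0.4 – 0.268 = 0.132 | 202–308 |
| Zero margin, one-sided 0.05 | 0.268 | 50–68 |
| Zero margin, two-sided 0.05 | 0.268 | 62–82 |

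The variants are pooled, unpooled and continuity-corrected; the Farrington-Manning score for the –0.4 rows; and arcsine and fully pooled for the zero-margin rows. Fisher's exact test with zero margin, two-sided, needs about 76 (80.7% power at 38 per arm). None gives 110 in total.

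The standard zero-margin, two-sided case: (1.960×0.5657 + 0.8416×0.5330)² / 0.268² = 1.5573² / 0.07182 = 33.8, so 34 per arm and 68 in total.

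**Settings that do return the number 110, each by changing something that section 2.4 states.**
- Power changed to 0.95, zero margin, two-sided: (1.1087 + 1.645×0.5330)² / 0.07182 = 1.9854² / 0.07182 = 54.9, so 55 per arm and 110 in total.
- Margin changed to a small positive value, power 0.80, unpooled: about 0.089 at one-sided 0.05 (0.2841×6.183 / 0.179² = 54.8 per arm), or about 0.067 at one-sided 0.025 (about 55 per arm).
- Label changed from total to per group: –0.4 as control minus experimental, one-sided 0.05, pooled: (1.645×0.5657 + 0.8416×0.5330)² / 0.132² = 1.3791² / 0.01742 = 109.2, so 110 per group and 220 in total.

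**What 120 patients deliver.** With 10% loss, 120×0.9 = 108, or 54 per arm.
- Two-sided chi-square of zero difference: (0.268×√54 – 1.1087)/0.5330 = 1.615, so power is 94.7% (exact binomial 96.0%). At 55 per arm it is 95.0%, and at 60 it is 96.5%.
- The same test with 54 per arm has 80% power for 88.8% v 66.6%, a difference of 22.2 points.
- –0.4 as control minus experimental, one-sided 0.05, 55 per arm, unpooled: (0.132×√55 – 1.645×0.5330)/0.5330 = 0.19, so power is about 58%. The pooled formula gives about 54%.

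**Dropout.** 110/0.9 = 122.2, while 120 less 10% leaves 108, 2 short of 110.

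**The case against.** A reader might go further and infer that the stated inputs need 68 patients, that 110 was computed at 95% power, that the stated power and N therefore cannot both be right, and that 120 can be kept with a change of wording only. The arithmetic behind 68 and 95% is correct, but the article does not support the inference.

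- The figure of 68 leaves out the stated –0.4 boundary and assumes a two-sided, uncorrected test that section 2.4 does not specify.
- The match at 95% is one back-fit among several, and the article gives both β = 0.2 and "test power = 0.8".
- A small positive margin would leave power and N both standing and make the boundary the error.
- The per-group match keeps the stated rates, α, power and boundary with its sign, and fails only on the word total. If that were the origin, the trial would be half its intended size under its own margin. It is no more established than the others, and the hypothesis behind it is not superiority of manual therapy.

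These objections limit the diagnosis. They do not remove the inconsistency, because each route to 110 changes something that section 2.4 states.

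On dropout, the text says about 10%, and 120 covers a loss of 10/120 = 8.3% from 110. That point is minor.

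**Conclusion.** The point holds as an inconsistency among the figures of section 2.4. At 80% power, 110 in total does not follow from the stated rates and α, either with the –0.4 boundary (about 8–18 or 202–308) or with no margin (about 50–82). The boundary also fits neither the superiority label nor the chi-square in section 2.9.

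Which figure is wrong cannot be settled from the article. The consequence depends on it: about 95% power for the pilot difference under the planned chi-square if two-sided, against about 58% at 110 in total if –0.4 was meant as control minus experimental with one-sided 0.05 (unpooled). These results take the pilot rates as true and rest on standard large-sample formulae. The exact calculation for the zero-difference case agrees within about 1.5 percentage points.

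**What to change.** State in section 2.4 the hypothesis, the direction of the difference, the margin, the sidedness of α and the test. Correct the figure that does not fit, so that the PASS output can be reproduced from the text.

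- **If the planned two-sided chi-square of zero difference is intended:** delete the –0.4 boundary and state that 120 are randomised and about 108 evaluable after 10% loss, giving about 95% power for 93.4% v 66.6%, or 80% power for about 22 points (88.8% v 66.6%). This costs a rewording of section 2.4.
- **If a margin is intended:** state it with its direction, bring the test in section 2.9 into line, and restate the power that 120 patients deliver under it. The text change is small, but whether 120 is enough cannot be judged until the margin is known.

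In either case, state the number evaluable after 10% loss as 108, or adjust the loss figure to match 110.
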